## Abstract

**Introduction:**

Integrated community healthcare Hubs may offer a ‘one stop shop’ for service users with complex health and social needs, and more efficiently use service resources. Various policy imperatives exist to implement Hub models of care, however, there is a dearth of research specifically evaluating Hubs targeted at families experiencing adversity. To contribute to building this evidence, we propose to co-design, test and evaluate integrated Hub models of care in two Australian community health services in low socioeconomic areas that serve families experiencing adversity: Wyndham Vale in Victoria and Marrickville in New South Wales.

**Methods and analysis:**

This multisite convergent mixed-methods study will run over three phases to (1) develop the initial Hub programme theory through formative research; (2) test and, then, (3) refine the Hub theory using empirical data. Phase 1 involves co-design of each Hub with caregivers, community members and practitioners. Phase 2 uses caregiver and Hub practitioner surveys at baseline, and 6 and 12 months after Hub implementation, and in-depth interviews at 12 months. Two stakeholder groups will be recruited: caregivers (n=100–200 per site) and Hub practitioners (n=20–30 per site). The intervention is a co-located Hub providing health, social, legal and community services with no comparator. The primary outcomes are caregiver-reported: (i) identification of, (ii) interventions received and/or (iii) referrals received for adversity from Hub practitioners. The study also assesses child, caregiver, practitioner and system outcomes including mental health, parenting, quality of life, care experience and service linkages. Primary and secondary outcomes will be assessed by examining change in proportions/means from baseline to 6 months, from 6 to 12 months and from baseline to 12 months. Service linkages will be analysed using social network analysis. Costs of Hub implementation and a health economics analysis of unmet need will be conducted. Thematic analysis will be employed to analyse qualitative data.

**Ethics and dissemination:**

Royal Children’s Hospital and Sydney Local Health District ethics committees have approved the study (HREC/62866/RCHM-2020). Participants and stakeholders will receive results through meetings, presentations and publications.

**Trial registration number:**

ISRCTN55495932.

Strengths and limitations of this studyThe ‘Child and Family Hub’ study is the first to our knowledge to co-design, test and evaluate two integrated Hub models of care for improving the detection of and response to family adversity for children aged 0–8 years.Implementation and evaluation in two community health services across two Australian states will maximise the generalisability of findings for different community and service contexts.The interdisciplinary conceptual framework underpinning this study strengthens its empirical robustness through synthesis of approaches from many disciplines to capture the complexity of the Hub models.The study has no comparison group which means that any observed changes for primary and secondary outcomes cannot be directly attributed to the Hub models of care.The English language inclusion criterion for participants limits our ability to engage culturally and linguistically diverse caregiver and practitioners.

## Introduction

### Family adversity and its negative impact on mental health

Interventions aimed at reducing or preventing the impact of adversity on children could avert a substantial proportion of the population burden of mental illness, and build on evidence demonstrating the health and economic benefits of investing early in life.^1^ Family adversity includes a range of adverse childhood experiences (ACEs) such as childhood maltreatment (eg, physical, verbal or sexual abuse), household dysfunction (eg, parental mental illness, family substance abuse), community dysfunction (eg, witnessing physical violence, discrimination), peer dysfunction (eg, stealing, bullying) and socio-economic deprivation.^2^ While family adversity can negatively impact a range of physical and mental health outcomes, its negative effects on children’s mental health are well established, increasing the risk of anxiety, depression and suicidality in childhood and across the life course.^3–8^ Further, exposure to multiple ACEs predicts greater odds of poorer mental versus physical health outcomes in adult life.^9^ Experiences of family adversity also negatively affect child’s neurological and physiological development and educational outcomes,^10^ which in turn lead to poor life-long health and mental health outcomes.^11^

### Detection and response to family adversity

As part of an Australian Centre of Research Excellence in Childhood Adversity and Mental Health, we will develop, test and evaluate an approach to improving the detection of and response to adversity in children aged 0–8 years and their families. Effective detection of adversity is crucial to the provision of appropriate, timely and evidence-based responses to the effects of adversity. However, major service barriers exist to the detection of, and responses to, adversity, including service time pressures, a lack of practitioner time, training and confidence in how to effectively discuss adversities, and practitioners’ concerns about causing harm.^5 12–14^ Family-level barriers also inhibit service access, including cognitive (ie, knowledge, awareness of services), psychological (ie, fear, shame and distrust of services), financial and structural barriers (ie, service availability, lengthy wait times, transport).^15–17^ These service access barriers are amplified for families experiencing multiple adversities who require supports from health, social, education and community service systems. These systems are often siloed which is likely to contribute to the low utilisation of services by these families.^18 19^ Hence, effective detection of, and responses to, adversity require intervention across multiple strata of intersectoral service systems.

### Integrated care for families experiencing adversity

Integrated care has the potential to overcome service fragmentation and respond to a range of holistic health and social needs for families and their children experiencing adversity. Integration is defined as care that: ‘connect[s] the healthcare system (acute, primary medical and skilled) with other human service systems (eg, long-term care, education and vocational and housing services) to improve outcomes (clinical, satisfaction and efficiency)’.^20^ Integrated care initiatives can increase uptake and ongoing engagement with child health services,^21 22^ improve child mental health outcomes^23 24^ and offer a cost-effective and acceptable service response for families.^25 26^ Integrated community healthcare Hubs have recently gained traction globally, driven by their appeal to offer a ‘one stop shop’ for service users with complex health and social needs, and to efficiently use service resources.^27^ While there is no single definition of a Hub, the term is often used to describe a centralised service that offers a range of co-located, integrated services from multiple sectors, with linkages to external services for community-based supports.^27 28^ Emerging evidence exists for outcomes of Hub models of care. For example, the Healthy Homes and Neighbourhoods (HHAN) initiative in Sydney, New South Wales (NSW), is a multi-component cross-agency care coordination network with a centralised Hub nested within a broader place-based initiative and has been shown to increase service access for families experiencing adversity.^29 30^

Various policy imperatives have been established to implement and evaluate Hub models of care for child and family mental health in Australia. These include the 2021 Royal Commission into Victoria’s Mental Health System (recommending implementation and evaluation of ‘infant, child and family health and well-being multidisciplinary community-based hubs’^31^ and the 2021 National Children’s Mental Health and Well-being Strategy.^32^ The increased rates of child mental health problems resulting from the COVID-19 pandemic underscore the need for accessible, effective mental health support in communities.^33^ However, there is a dearth of research specifically evaluating Hub models of integrated care for families experiencing adversity with a particular focus on child mental health. Extant research also does not specify when and how integration of care occurs within Hubs across the layers of a service ecological system (ie, clinical, professional, organisational and systems integration^31^), and which types of integration in co-located Hub models drive observed changes for children and families.

### The current study

To contribute to building this evidence, we propose to co-design, test and evaluate integrated Hub models of care in two Australian community healthcare services in low socioeconomic, metropolitan areas that serve families experiencing adversity, that is, Wyndham Vale in Victoria and Marrickville in NSW. Twenty-three per cent of children in Wyndham and 14.6% of children in Marrickville are developmentally vulnerable in one or more domains of the Australian Early Development Census.^34^ In this study, we define a Hub as a co-located service providing an intersectoral health, social, legal and community response to family adversity. The Wyndham Vale site is a Hub in a local government area and the Marrickville site is a Hub nested within a broader place-based initiative. Co-design of a Hub at each site will involve caregivers, community members and service providers. The evidence generated from this study is crucial for increasing the conceptual precision around integrated Hub models of care and in addressing the evidence gap on their effectiveness for detecting and responding to family adversity and promoting positive child and caregiver mental health.

### Study aims and objectives

#### Aim

To co-design, test and evaluate integrated Child and Family Hub models for detecting and responding to family adversity in children aged 0–8 years and their families in Wyndham Vale, Victoria, and Marrickville, NSW.To formulate a realist-informed programme theory of how, why, for whom and under what conditions the Hubs work to detect and respond to family adversity.

#### Objectives

1. To assess the impact of the Hub models on:

##### Primary outcomes

1.1. caregiver-reported (i) identification of, (ii) interventions received and/or (iii) referrals received for adversity from Hub practitioners.

##### Secondary outcomes

1.2. Hub practitioner-reported (i) identification of, (ii) interventions delivered and/or (iii) referrals provided for adversity,1.3. Caregiver-reported uptake of referrals,1.4. Child and caregiver mental health,1.5. Infant temperament,1.6. Child and caregiver global health,1.7. Caregiver parenting,1.8. Caregiver quality of life,1.9. Caregiver personal well-being outcomes,1.10. Caregiver experience of care,1.11. Practitioner experience including confidence and competence in detecting and responding to adversity,1.12. Linkages between intersectoral Hub practitioners, and

2. To determine the costs of implementing the Hub models, and

3. To determine the extent that the Hub models are providing the intended service option (ie, acceptability, feasibility and fidelity to the initial Hub programme theory).

Reporting in this protocol is based on the Strengthening the Reporting of Observational Studies in Epidemiology (STROBE) Statement.^35^

## Methods and analysis

This study is a multisite implementation and evaluation project that employs a convergent mixed-methods design conducted over three research phases displayed in figure 1 below. Quantitative and qualitative data will be collected in parallel and integrated during data analysis and interpretation.^36^

**Figure 1 F1:**
[figure not shown]
Evaluation processes and phases. CIMO, context-intervention-mechanism-outcome.

### Interdisciplinary conceptual framework

The study is underpinned by an interdisciplinary conceptual framework drawn from implementation science, critical realism, improvement science and collaborative co-design paradigms.^37–44^ Interdisciplinary research strengthens empirical robustness through synthesis of approaches from many disciplines, and has been shown to increase the uptake of research into policy and practice.^45^ The approach and rationale for the interdisciplinary framework in order of importance for this study are:

*Implementation science*: Given the focus of our inquiry on complex Hub interventions, key implementation science frameworks form the basis of our process and outcomes evaluation, including our framing and synthesis of context using the Consolidated Framework for Implementation Research (CFIR).^42^*Critical realism and realist evaluation*: We draw on elements of critical realism and realist evaluation, a form of theory-driven evaluation, to theorise and examine ‘what works, for whom, under what circumstances and how’.^46–49^ Realist evaluation assumes that interactions between context and intervention mechanisms produce the outcomes of an intervention.^47 48 50 51^ We focus our inquiry on the key context-intervention-mechanism-outcome (CIMO) configurations discussed below. We complement realist evaluation methods with critical realism^52 53^ to understand the historical aspects of each locality and how this history influences the design and workings of each new Hub. This overcomes a key shortcoming of realist evaluation, that is, under theorising the multiple levels of social reality surrounding each Hub.^54 55^*Improvement science*: We use improvement science methods to implement agile learning and testing cycles that will iterate the Hub models and embed learning systems into practice.^43^*Collaborative co-design:* We use these principles and methods to co-design the Hub models and promote stakeholder engagement throughout the research process.

Figure 1 displays the three study phases based on Pawson and Tilley’s^46^ realist evaluation framework: (1) Development of the initial Hub programme theory through formative research; (2) Testing of the initial Hub theory using empirical data; and (3) Refinement of the initial Hub theory.

### Study phase 1: development of initial Hub programme theory through formative research

The initial Hub programme theory was developed through an intensive formative research phase during which we collected contextual information and co-designed the Hub models with intersectoral (eg, health, social, legal and education) practitioners and caregivers from each local community. This phase occurred from October 2020 to June 2021 in Victoria and January to August 2021 in NSW. First, a historical and current needs assessment of the health, social, legal and community contexts of each site was conducted using qualitative data from online group discussions, individual interviews and meetings with key stakeholders including intersectoral practitioners (ie, from health, social, legal and community sectors) and caregivers. We used CFIR^42^ to capture and synthesise these data into barriers and enablers across the outer setting, inner setting, individual level, process and intervention components.

Second, we reviewed the HHAN programme theories and other relevant realist literature focused on integrated care for children and families experiencing adversity^23 30 56–59^ to identify key CIMO configurations relevant to the Hubs. HHAN provided a useful starting point because our study builds on the HHAN model of care. For pragmatic reasons, we focus the process and outcome evaluation in this study on three key mechanisms and associated CIMO configurations in the initial programme theory. Namely, (1) trust between caregivers and the service/practitioners, and between practitioners, (2) knowledge acquisition and motivation of practitioners and (3) perceived benefits of collaboration by practitioners. Figure 2 displays the initial realist-informed programme theory. We then formulated the logic model displayed in figure 3 proposing how the Hub models will be investigated and are theorised to contribute to outcomes. The logic model includes how immediate outcomes, that is, increased detection and response to adversity are hypothesised to lead to our intended outcomes, including increased uptake of services and improved child and caregiver mental health and caregiver quality of life.

**Figure 2 F2:**
[figure not shown]
Initial Hub programme theory from a realist perspective.

**Figure 3 F3:**
[figure not shown]
Logic model proposing how the Hub models will be investigated. PDSA, Plan-Do-Study-Act.

Third, the Hub models were then developed and refined through a collaborative co-design process with intersectoral practitioners, caregivers and children at each site. The co-design process focused on the client journey through each proposed Hub and the workforce capacities and infrastructure needed to support implementation of the Hub. In Wyndham Vale, the Hub model was co-designed through an intensive 10-week series of co-design workshops and consultations with local caregivers and practitioners using human-centred design processes.^37–39^ In Marrickville, the Hub model will be co-designed through focus group discussions and workshops employing the Nominal Group Technique consensus method^60^ to prioritise and develop implementation strategies. Different approaches to co-design are adopted that reflect the capacity, capabilities and preferences for engagement of the research team and co-design partners at each site.

The theorised Hub models comprise:

*Family and community partnerships*: intentional creation and strengthening of connections between the Hub and caregivers, community groups and individuals. These partnerships also involve Hub practitioners working in partnership with families during clinical practice.*Entry to the Hub:* a *‘*no wrong door’ approach in which caregivers are safely engaged in a conversation about adversity and provided with any necessary support and/or referrals regardless of how they enter the Hub.*Workforce development*: workforce capacity building and training of Hub practitioners to engage families in a safe and respectful conversation to identify adversities and connect families to relevant support.*Case-based discussions:* monthly professional development with intersectoral Hub practitioners to embed training learnings into practice and facilitate between-practitioner referrals (ie, ‘warm referrals’).*Referral pathways into and out of the Hub*: systematic mapping of available health, community and social sector supports and services in the local area, linked to training of Hub practitioners to use this information in their practice.*Care navigation*: In Wyndham Vale, a Well-being Coordinator will support caregivers to identify the holistic needs of their child and/or family and assist them to navigate relevant services and supports in the community, social and health sectors. In Marrickville, care navigation is likely to include a Well-being Coordinator or a virtual application for caregivers that provides a risk stratification and recommendations of relevant services.

### Study phase 2: testing of initial Hub theory using empirical data

We will empirically test the initial programme theory for the Hubs through a mixed-methods process with 6 and 12 months outcomes evaluation. The evaluation aims to assess for whom, how and why the Hub models had an impact (if any) in the two different contexts of Wyndham Vale and Marrickville across the child, caregiver, practitioner and system level outcomes specified in figures 2 and 3, table 1 and ‘Outcomes Assessment’ below.

**Table 1 T1:** Primary and secondary outcomes

Primary outcomes		Baseline assessment		6 and 12 months post Hub implementation begins	
		**Caregiver survey**	**Practitioner survey**	**Caregiver survey**	**Practitioner survey**
*Caregiver*					
Identification of adversity	Increase in the proportion of caregivers who report being asked by a service provider about adversity in the past 6 months.	X		X	
Intervention for adversity	Increase in the proportion of caregivers who report spending extra time with or receiving an intervention from a Hub service provider for adversity in the past 6 months.	X		X	
Referrals for adversity	Increase in the proportion of caregivers who report receiving a referral to an intersectoral service for adversity in the past 6 months.	X		X	

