Caregiver experience	Caregiver reported acceptability and feasibility of the Hub; Increase in the proportion of caregivers who report their satisfaction with Hub care as measured by three items from the Australia Bureau of Statistics Patient Experiences in Australia Survey.^85^	X		X	
Personal well-being	Increase in mean scores of caregiver-reported personal well-being outcomes measured by the Personal Well-being Index; 7 items.^86^	X		X	
*Practitioner*					
Identification of adversity	Increase in the proportion of practitioners who report asking about adversity in the past 6 months.		X		X
Intervention for adversity	Increase in the proportion of practitioners who report spending extra time or providing an intervention for adversity in the past 6 months.		X		X
Referrals for adversity	Increase in the proportion of practitioners who report referring caregivers to an intersectoral service for adversity in the past 6 months.		X		X
Practitioner experience	Practitioner reported acceptability and feasibility of the Hub; Increase in the proportion of practitioners who report feeling confident and competent to detect and support families experiencing adversity.		X		X
*System level*					
Strength and structure of intersectoral service linkages	Increase in the number and strength of service linkages between Hub practitioners as assessed through social network analysis (SNA) indicators for network density, degree, centrality and betweenness, and map of linkages between Hub practitioners based on i) contact, (ii) referrals to, (iii) referrals from, and (iv) quality of the relationship.^68–71^		X		X
Health economics outcomes	Costs of implementation of the Hub models, caregiver-reported intersectoral service usage and value of unmet need.	X		X	

*Caregivers with more than one child will respond to questions pertaining to one child in their family based on the child they are most concerned about.

†The ASQ-SE is limited by its design as a screening tool that may not be a sensitive outcome measure. The measure is used in this study because it more directly measures mental health and well-being than the ASQ.

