#### Data collection

##### Caregiver and Hub practitioner surveys

The Caregiver and Hub practitioner baseline and outcome surveys consisting of the measures outlined in table 1 and available in online supplemental file 1 will be built in Research Electronic Data Capture (REDCap)^63^ hosted by Murdoch Children’s Research Institute. After completing an informed consent process, caregivers can complete the baseline survey: (i) in paper form, (ii) over the telephone with a researcher or (iii) online. Practitioners will complete the practitioner baseline survey in paper form or online via REDCap. The practitioner survey will be sent towards the end of baseline data collection to minimise the potential impact of the survey on clinical practice prior to the Hub testing period. Caregiver and practitioner participants will be contacted by telephone, email or text message by the research team 6 and 12 months after the Hub implementation begins and invited to complete the follow-up survey.

10.1136/bmjopen-2021-055431.supp1Supplementary data

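### The three primary outcomes in Table 1 name different providers, contradict objective 1.1, and leave Hub care undefined at a baseline taken before the Hub starts

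*Protocol article*

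**What the plan says.** - **Objective 1.1** (Objectives, Primary outcomes) gives one source for all three components: "caregiver-reported (i) identification of, (ii) interventions received and/or (iii) referrals received for adversity from Hub practitioners". The abstract (Methods and analysis) says the same.
- **Table 1, identification:** caregivers who "report being asked by a service provider about adversity in the past 6 months".
- **Table 1, intervention:** caregivers reporting extra time or "receiving an intervention from a Hub service provider for adversity in the past 6 months".
- **Table 1, referral:** caregivers "who report receiving a referral to an intersectoral service for adversity in the past 6 months". The destination is named and the referrer is not.
- **Table 1, Caregiver experience:** "Increase in the proportion of caregivers who report their satisfaction with Hub care", in the same row as acceptability and feasibility of the Hub.

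All four rows are marked for the caregiver survey at baseline and again at 6 and 12 months after implementation begins. The section on caregiver and Hub practitioner surveys places baseline before the Hub is tested: the practitioner survey goes out late in baseline collection to "minimise the potential impact of the survey on clinical practice prior to the Hub testing period". Quantitative data analysis then examines change from baseline to 6 months, 6 to 12 months, and baseline to 12 months. The strengths and limitations box states that there is no comparison group.

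**The concern.** Two separate problems arise.

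First, the primary endpoint is defined in two incompatible ways. Under objective 1.1 a caregiver counts only if a Hub practitioner asked, intervened or referred. Under Table 1 a caregiver who was asked about adversity by a provider elsewhere counts for identification, and one referred by anybody counts for referral. A change in outside care would then be reported as Hub performance.

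Second, the intervention item depends on the caregiver classing a provider as a Hub provider. At baseline the 6-month look-back lies wholly before implementation. At follow-up the Hub is running under that name. If the same care from the same staff is more readily called Hub care later on, the proportion rises with no change in care. Satisfaction with Hub care has a similar difficulty at baseline, although Table 1 gives it no look-back period.

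With no comparison group, change from baseline carries most of the weight in judging impact. The primary outcomes at 6 and 12 months are also the variables whose association with mental health and quality of life is to be tested by linear regression, so their definition affects those analyses too.

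**Working it through.** The article gives no sample size calculation, baseline rate or significance level, so there is no figure of its own to reproduce. The check is a comparison of texts, followed by an illustration of size.

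**Step 1. Provider scope, side by side**

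| Outcome | Objective 1.1 and abstract | Table 1 |
|---|---|---|
| Identification | Hub practitioners | any service provider |
| Intervention | Hub practitioners | Hub service provider |
| Referral | Hub practitioners | referrer not named |

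Only the intervention row agrees with the objective.

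**Step 2. What Hub means at baseline**

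- *Existing sites and staff.* The current study sets the Hubs in two community healthcare services. Eligible caregivers are those using services provided in the Hub (Caregivers). They are recruited in Hub waiting rooms and through Hub practitioners, and practitioners working in each Hub are invited before the workforce training (Recruitment and consent).
- *The new model.* The abstract calls the co-located Hub the intervention. Study phase 1 speaks of proposed Hubs and lists components to be introduced, including workforce training, case-based discussions and, at Wyndham Vale, a Well-being Coordinator.

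Nothing in the article says which meaning applies to the intervention item or the satisfaction items at baseline.

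**Step 3. Size of the possible artefact in the intervention outcome**

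Assumptions, none taken from the documents: the true proportion *p* receiving an intervention from these services is the same at baseline and follow-up; a share *f* of baseline care is recognised as Hub care; all follow-up care is.

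Apparent change = *p* − *pf* = *p*(1 − *f*).

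For illustration only, the chance of a significant rise uses an unpaired two-proportion test at two-sided 5%, with *n* caregivers at each wave:

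Φ{[Δ − 1.96√(2p̄(1 − p̄)/n)] / √[(p_b(1 − p_b) + p_f(1 − p_f))/n]}

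Here p_b = *pf* is the baseline proportion, p_f = *p* the follow-up proportion, p̄ their mean and Δ their difference. The values n = 100 and 200 span the planned range per site, and 200 to 400 the total.

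Worked case, *p* = 0.30, *f* = 0.5, *n* = 100: p_b = 0.15, p_f = 0.30, p̄ = 0.225. The null standard error is √(2 × 0.225 × 0.775/100) = 0.0591 and the other is √((0.1275 + 0.21)/100) = 0.0581. Then (0.15 − 1.96 × 0.0591)/0.0581 = 0.59, and Φ(0.59) = 0.72.

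| *p* | *f* | Apparent change (points) | n = 100 | n = 200 | n = 400 |
|---|---|---|---|---|---|
| 0.30 | 1.00 | 0 | 0.025 | 0.025 | 0.025 |
| 0.30 | 0.90 | +3 | 0.07 | 0.10 | 0.15 |
| 0.30 | 0.75 | +7.5 | 0.22 | 0.40 | 0.67 |
| 0.30 | 0.50 | +15 | 0.72 | 0.95 | 1.00 |
| 0.30 | 0 | +30 | 1.00 | 1.00 | 1.00 |
| 0.10 | 0.50 | +5 | 0.27 | 0.48 | 0.77 |
| 0.10 | 0 | +10 | 0.91 | 1.00 | 1.00 |

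The artefact runs from nil to the whole of *p*, and under these assumptions it is never negative. The surveys are repeated measures, so the unpaired test is only an approximation, and loss to follow-up is ignored.

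**The case against.** The strongest reply is that Hub providers are already there. The article applies the term to waiting rooms, services and practitioners seeing clients before implementation; what is new is mainly the way they work. On that reading *f* is close to 1 and the intervention item is comparable across waves. This reply defeats a stronger reading that a reader might infer: that baseline is zero by construction and a rise is nearly guaranteed. With a true structural zero, an exact McNemar test would reach p = 2 × 0.5⁶ = 0.031 once six caregivers said yes at follow-up (five give 0.0625). The documents do not establish such a zero, and the plan specifies neither that test nor a significance level.

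Three further limits are fair:

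- Different providers across the three items do not by themselves spoil comparison over time, because Table 1 gives each item one wording for all waves. The fault there is disagreement with the objective and between items.
- The change from 6 to 12 months lies wholly after implementation and is untouched by baseline labelling. The practitioner-reported versions of these outcomes in Table 1 do not depend on a caregiver's use of the label.
- The survey items are in online supplemental file 1, which is not at hand, and may already name the services. For satisfaction, a respondent who sees no Hub at baseline is more likely to give a not-applicable answer than to produce an artificial rise.

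What remains is the contradiction between Table 1 and objective 1.1, which none of this removes, and the double meaning of Hub, which the article leaves open at the wave where it matters. If the survey items prove consistent, Table 1 still misstates the primary outcomes.

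**Conclusion.** The point holds in this form. The primary outcomes are defined inconsistently: the objective and abstract require Hub practitioners for all three, and Table 1 requires them for one. Followed as written, Table 1 would let care outside the Hub move identification and referral, in either direction, under an objective that speaks of Hub practitioners.

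The intervention outcome is open to upward bias of *p*(1 − *f*). At an assumed *p* of 30% that is 15 points if half of baseline care is recognised as Hub care, 7.5 points if three quarters is, and nil if all existing site staff count. Neither *p* nor *f* can be obtained from the documents, so the bias is possible and not demonstrated. Satisfaction with Hub care, and acceptability and feasibility of the Hub, lack a defined object at baseline; the likely result is uninterpretable baseline answers.

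This is more than missing detail, because it concerns the primary endpoint in a single-group study, and analysis cannot recover which provider a caregiver had in mind if the survey did not ask.

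**What to change.** 1. Define one provider set that exists at every wave: the named community health service at each site and its listed partner services.
2. Use that set, worded identically at baseline, 6 and 12 months, in all three primary items and the three satisfaction items.
3. Align objective 1.1, the abstract and Table 1 with that definition.
4. Ask about any other provider in a separate item, so that care outside the Hub can be seen and reported apart.
5. Collect Hub-specific acceptability and feasibility at 6 and 12 months only, and remove their baseline mark in Table 1.
6. Check the survey in supplemental file 1 first. If its items already name the services consistently, correcting the objective, abstract and table may suffice for the primary items.

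The cost is minor rewording and an ethics amendment. If baseline data have already been collected, the wording cannot be changed in retrospect: classify providers by named service where this was recorded, and report the change in the intervention outcome descriptively, with the labelling caveat stated.
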